### Study population

Patients will be informed about the study as part of the initial consultation for radiation therapy.

#### Inclusion criteria

Patients meeting all of the following criteria will be considered for admission to the trial:

Written informed consent.Patient older than 18 years.Tumor or metastases in the brain.Immobilization with stereotactic mask (basic cranial mask; Brainlab, Munich, Germany).Treatment on stereotactic linear accelerator (2.5 mm leafs) equipped with 2D/2D X-ray system.

#### Exclusion criteria

Patients presenting with any of the following criteria will not be included in the trial:

Metal in the body, metal implants, pacemakers or other patient-specific factors that are a contraindication to an MRI scan.Metal implants, pacemakers or other patient-specific factors associated with increased risk from an MRI scan.Renal insufficiency (eGFR < 60 ml/min), allergy or other patient-specific factors that constitute a contraindication to contrast administration.Renal insufficiency (eGFR < 60 ml/min), allergy or other patient-specific factors associated with an increased risk from contrast administration.Patients who are institutionalized in care facilities, prisons or other supervised facilities.Patients under guardianship.Non-consenting patients.Pregnant or breastfeeding patients.

### Study objectives

The main objective of the study is the investigation of the feasibility of an MRI-only workflow using synthetic CT for the treatment of patients with tumors and metastases in the brain. The study will investigate what proportion of treatments can be completed in an MRI-only workflow. The main hypothesis is that 90% of the patients can be successfully treated in an MRI-only workflow, as will be derived in more detail in Sect. 2.5.

The following parameters will be collected as secondary study objectives:

Which parameters lead to a change from MRI-only workflow to standard workflow?Documentation of all comparative parameters between MRI-only and standard workflow.Evaluation of the intra-MRI registration data, i.e. comparison of MRI images taken at start vs. end of an MR imaging slot.Evaluation of OAR contouring accuracy on MRI data.

### Study plan

During the course of this study the entire treatment procedure is identical for study patients and patients in the standard workflow; it differs only in terms of the data used for treatment planning. As shown in Fig. 1, the accuracy and feasibility of the sCT-based workflow compared to the standard workflow is checked at several points in the treatment process and, in the event of excessive deviations, the treatment is continued according to the clinical standard.

To ensure geometric accuracy of the MRI system a daily system check, including gradient sensitivity, spatial integrity and shimming/ magnetic field homogeneity is performed. Additionally, a monthly check of the gradient non-linearity related distortion, with a dedicated phantom. Also a QA of all coils is regularly performed. The QA program is based on the DEGRO recommendations [30].

The following verifications are investigated, with the detailed parameters/checks listed in Table 1:

**Table 1 Tab1:** Overview of verifications throughout the treatment workflow. In case a verification fails, the patient is transferred from the MRI-only workflow to the standard workflow based on CT

No.	Verification criterion
1	Can the sCT be generated and is the sCT clinically utilizable?
2	Are the three rotations needed for CT-MRI registration each ≤ 3°?
3	Can a treatment plan be generated and verified using the sCT?
4	Is the dosimetric difference between sCT- and CT-based treatment plans in the PTV ≤ 3%?
5	Is the dosimetric difference between the sCT- and CT-based treatment plans in affected OARs (receiving > 10% of prescribed dose) ≤ 3%?
6	Are the couch correction parameters during patient positioning in the rotational degrees of freedom ≤ 3°?

**Verification 1** aims to ascertain the feasibility of sCT generation and its potential clinical utility. In the course of this study, the patient is subjected to a comprehensive and standardized imaging procedure, encompassing MRI (comprising all sequences of a standard treatment) and CT scans [24, 31]. Subsequently, an sCT is generated exclusively through the reconstruction of MRI data.

As a next step, the process involves registering MRI and CT scans as in the standard workflow in a specialized medical treatment planning system (syngo.via RT Image Suite, VB60a or higher, Siemens Healthineers, Erlangen, Germany). Additionally, the registration process is validated in a second treatment planning system (RayStation v12A or higher, RaySearch, Stockholm, Sweden). **Verification 2** is conducted to assess the degree of rotation during the registration process, i.e. if positioning the patient in the MR scanner was achieved as intended. If all rotation angles are found to be equal to or less than 3°, the workflow remains based on sCT data. However, if both planning systems calculate rotation angles greater than 3°, it is recommended to switch to a CT-based standard workflow. If both registration algorithms calculate different angles, one greater than and one less than 3°, a physician’s clinical manual registration is also used for decision making.

Furthermore, as **additional investigation 1**, the MRI images used for generating the sCT (vibe-DIXON) are registered with the MRI images obtained from the SPACE sequence (utilized for tumor segmentation). The objective is to detect potential changes that might occur during the approximately 30-minute MRI acquisition period, which is specific to this study and does not impact the ongoing treatment.

In the current standard workflow, the clinical target volume (CTV) is contoured on the MRI dataset and transferred to the planning CT. OARs, however, are automatically contoured on the planning CT using the deep learning solution DirectORGANS (Siemens Healthineers GmbH, Erlangen, Germany) that is directly embedded into the CT scanner. In the study, OAR have to be contoured manually based on the MRI data. Retrospectively, as **additional investigation 2**, these OAR structures will be compared with those automatically segmented on CT images (comparison measures include: DICE coefficient and Hausdorff distance).

**Verification 3** is aiming to assess the technical feasibility of treatment planning using the sCT approach, i.e. if the treatment plan can be generated, verified, and transmitted to the record and verify system. The physical treatment planning system used is RayStation (v12A or higher, RaySearch, Stockholm, Sweden). The verification process entails multiple aspects, including the creation of sCT images, consideration of the mask support [27] and verification of the treatment plan (currently Mobius3D, Varian, Darmstadt, Germany and/or ArcCHECK, SunNuclear, Neu-Isenburg, Germany).

For quantitative verification of the sCT-based treatment plan, an equivalent CT-based treatment plan is created by transferring the plan to the CT followed by dose re-calculation using the same physical treatment planning system as mentioned above. The aim of **Verification 4** is to verify the dosimetric equivalence of CT- and sCT-based planning methods. It focuses on assessing the dose difference within the PTV, aiming to ensure that any variations between the CT- and sCT-based plans do not exceed 3% (ΔD_50_ < 3%), where D_50_ refers to the dose covering 50% of the PTV. This rigorous evaluation is crucial to determine the accuracy and consistency of the sCT-based approach in delivering the intended radiation dose to the target volume.

Similarly, **Verification 5** investigates the dose difference in OARs. The objective is to ensure that affected OAR, i.e. OAR which receive > 10% of the prescribed dose, also exhibit dose differences within the acceptable threshold of 3% (i.e. ΔD_50_ < 3% and ΔD_0.01ccm_ <3%). This assessment provides vital insights into the safety and efficacy of the sCT-based radiation planning in sparing at-risk structures from potential damages.

Verification 4 and Verification 5 aim to validate the reliability and clinical suitability of the sCT-based radiation planning method, ensuring that it achieves dosimetric equivalence with the established CT-based approach. This thorough analysis contributes to the overall confidence in implementing sCT-based radiation planning in clinical practice.

As in the standard workflow, patient positioning at the linear accelerator is conducted using the 2D/2D non-coplanar x-ray positioning technique (ExacTrac v6.0.6, Brainlab, Munich, Germany). In case of the MRI-only workflow, the positioning process relies on sCT-based DRRs and thus DRRs reflecting the patient positioning at the MRI acquisition. **Verification 6** focuses on the evaluation of the calculated table rotation for all three directions of rotation. The primary objective is to ensure that the table rotation values do not exceed 3° and that the DRRs calculated from the sCT, can be used correctly. Together with verification 2 this approach serves as a doublecheck that the positioning at the MRI was correct, since positioning of the patient at the MRI, linac and CT should be reproducible and should not differ from each other.

### Statistical design

To estimate the required patient number, the MRI images of all brain stereotactic treatments at the stereotactic linear accelerator of our center, who received a dedicated RT simulation MRI from the last 3 years were examined retrospectively for artifacts and other exclusion criteria of an sCT workflow. The results showed that 91% of the 45 patients would have been suitable for an sCT workflow. 5% of patients were not suitable due to claustrophobia. A further 4% of patients were not eligible because they had metal artifacts on the skull due to surgery or had a glass eye, for example. According to Masitho et al. [25], further exclusion based on dose deviations in OARs or PTVs in comparison to the planning CT are not to be expected. Only one patient was found to have problems with sCT reconstruction. Thus, the overall feasibility of sCTs workflows is estimated to be 90%.

The case number calculation for the study is based on a one-stage design for pilot studies by Fleming [32]. The calculation is based on the following general conditions:

According to the information of the retrospective analysis of all stereotactic brain patients in the past three years, the application of the sCT workflow is considered feasible if the study procedure described above proves to be feasible accordingly. It is expected and postulated for a positive evaluation of the study outcome that this is the case in 90% of patients.The sCT workflow, on the other hand, would be considered not sufficiently feasible if the feasibility rate was 75% or less.The probability of erroneously assessing the experimental intervention as feasible even though the true feasibility is at/below 75% (α-error) is said to be only 5%.The probability of erroneously discarding the experimental measure as not sufficiently feasible although the true feasibility rate is 90% or more (β-error) should be no more than 10%, corresponding to a power of the study of 90%.

According to these parameters *n* = 54 patients who can be evaluated in terms of feasibility are needed.

Patients who show a violation of the inclusion criteria at the time of inclusion in the study (“non-eligible”) are excluded from the statistical analysis (e.g. Unsuitable for MRI due to metallic implants, withdrawal of consent, immobilization without stereotactic mask). These cases will only be reported casuistically. Which patients with serious protocol violations fall into this category is decided prospectively in a “blind review” before the analyses are carried out.

All other patients are included in the evaluation of the primary objective criterion in the sense of an “intention-to-treat analysis” (ITT).

The primary study objective criterion is calculated by dividing the number of ITT patients in whom the experimental method was found to be feasible by the total number of ITT patients. The exact one-sided 95% and 90% confidence intervals are calculated for the resulting rate.

The analysis of all other parameters is done descriptively, depending on the data type, with frequencies, means, medians, ranges of values and/or confidence intervals, if applicable.

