**Methods:**

A total of 54 patients with an indication for radiation treatment of the brain and stereotactic mask immobilization will be recruited. All study patients will receive standard therapy and imaging including both CT and MRI. All patients will receive dedicated RT-MRI scans in treatment position. An sCT will be reconstructed from an acquired MRI DIXON-sequence using a commercially available deep learning solution on which subsequent radiotherapy planning will be performed. Through multiple quality assurance (QA) measures and reviews during the course of the study, the feasibility of an MRI-only workflow and comparative parameters between sCT and standard CT workflow will be investigated holistically. These QA measures include feasibility and quality of image guidance (IGRT) at the linear accelerator using sCT derived digitally reconstructed radiographs in addition to potential dosimetric deviations between the CT and sCT plan. The aim of this clinical study is to establish a brain MRI-only workflow as well as to identify risks and QA mechanisms to ensure a safe integration of deep learning-based sCT into radiotherapy planning and delivery.

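### With the exact analysis that is planned, no success cut-off at n = 54 meets both the stated α of 5% and the stated power of 90%

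*Protocol article*

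**What the plan says.** All of this stands in the Statistical design section of the protocol article.

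- **Design.** The case number is "based on a one-stage design for pilot studies by Fleming".
- **Null rate.** The workflow "would be considered not sufficiently feasible if the feasibility rate was 75% or less".
- **Target rate.** 90% of patients.
- **Error rates.** The chance of wrongly calling the workflow feasible at or below 75% is set at 5%. The chance of wrongly discarding it at a true rate of 90% or more "should be no more than 10%, corresponding to a power of the study of 90" per cent.
- **Size.** The conclusion is that "54 patients who can be evaluated in terms of feasibility are needed".
- **Analysis.** The primary rate is the number of feasible cases divided by the number of patients in the intention-to-treat set. "The exact one-sided 95% and 90% confidence intervals are calculated for the resulting rate".

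The section gives no minimum number of successes out of 54. It does not say whether the 95% interval, the 90% interval or a separate test decides the outcome.

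**The concern.** The sample size and the analysis use different probability models. The size comes from a normal approximation to the binomial; the analysis is exact. At about 50 patients and rates of 75% to 90%, the binomial distribution is coarse. Moving the cut-off by one patient shifts α by more than two percentage points and power by about eight, so the approximate design figures need not carry over to the exact analysis.

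Two things are at stake. The first is whether the error rates stated for the primary objective are the ones the study will have. The second is how a result of 46 of 54 (85.2%) would be judged: the approximate test calls it a success, while the exact one-sided 95% interval still contains 75%. A plan should not leave such a result open to two verdicts.

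**Working it through.** **Inputs**, all from the Statistical design section: null rate p0 = 0.75, target rate p1 = 0.90, one-sided α = 0.05, power 0.90, one stage, n = 54 evaluable, exact one-sided 95% and 90% intervals.

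**Step 1: reproduce the plan's figure.** The one-sample normal approximation is

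n = [(z0.95 √(p0(1 − p0)) + z0.90 √(p1(1 − p1))) / (p1 − p0)]²

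= [(1.645 × 0.4330 + 1.282 × 0.3000) / 0.15]² = 53.46, rounded up to 54.

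The stated size therefore reproduces. On the same approximation, power at n = 54 is 90.3%.

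**Step 2: the cut-off of the approximate test.** Under the null rate the expected count is 54 × 0.75 = 40.5, with standard deviation √(54 × 0.75 × 0.25) = 3.182. The boundary is 40.5 + 1.645 × 3.182 = 45.73, so success would need at least 46 of 54.

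**Step 3: exact properties at n = 54.** For cut-off r, exact α is P(X ≥ r) with X binomial(54, 0.75), and exact power is P(X ≥ r) with X binomial(54, 0.90). The lower limits are the exact (Clopper-Pearson) one-sided limits when exactly r successes are seen.

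| Cut-off r | Exact α | Exact power | 95% lower limit | 90% lower limit |
|---|---|---|---|---|
| 45 | 10.1% | 96.0% | 72.7% | 74.97% |
| 46 | 5.25% | 91.4% | 74.85% | 77.1% |
| 47 | 2.41% | 83.2% | 77.0% | 79.2% |
| 48 | 0.96% | 70.7% | 79.2% | 81.3% |

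Both α and power fall as r rises. An α of at most 5% needs r of at least 47; power of at least 90% needs r of at most 46. No cut-off does both.

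**Step 4: link to the planned intervals.** The first count whose exact 95% lower limit exceeds 75% is 47. The first whose exact 90% lower limit exceeds 75% is 46. Deciding by the 95% interval gives α 2.41% and power 83.2%; deciding by the 90% interval gives α 5.25% and power 91.4%.

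**Step 5: neighbouring sizes.** For each n, take the smallest cut-off with exact α of at most 5%.

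| Evaluable n | Cut-off | Exact α | Exact power |
|---|---|---|---|
| 50 | 43 | 4.53% | 87.8% |
| 53 | 46 | 2.83% | 84.4% |
| 54 | 47 | 2.41% | 83.2% |
| 55 | 47 | 4.54% | 90.6% |
| 56 | 48 | 3.92% | 89.7% |
| 59 | 51 | 2.48% | 86.9% |
| 60 | 51 | 4.52% | 92.7% |
| 63 | 54 | 2.93% | 90.5% |

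The smallest size that meets both targets is 55. Power drops below 90% again at 56 to 59 and at 64. It is at least 90% at 60 to 63 and at every size from 65 to 120, the upper end of the range checked.

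**The case against.** The best defence is that the article names a one-stage Fleming design, which is an approximate method, and that 54 follows from it correctly. The cut-off that belongs to it is 46 of 54, where the approximate test gives z = (46 − 40.5)/3.182 = 1.73, p = 0.042. Exact power there is 91.4%, so the power target is met, and the only departure is 0.25 percentage points of α. The intervals can be read as estimates reported beside the test. A condensed article may also leave the cut-off itself to the full protocol.

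Much of this stands. A reader might infer that 54 is an arithmetic error; it is not. A reader might also take 83.2% as the study's power without condition. The article does not support that either, because it says only that two intervals are calculated and does not make the 95% limit the success criterion.

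The defence does not remove the inconsistency. Sample size, error rates and exact analysis are all stated in this section, and whichever cut-off a fuller document names, one of the two stated rates is missed at n = 54. The defence also rests on 46 of 54, a result for which the planned exact 95% interval does not exclude 75%.

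A still lower power might be inferred from the retrospective series: 91% of 45 is about 41 patients, and taking away the one reconstruction problem leaves 40 of 45. The text does not clearly place that patient among the 45, since the sentence follows the cited dosimetric study, and the section itself concludes 90%. No power figure should be built on that.

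**Conclusion.** The point holds in this form: 54 is the normal-approximation size, and under the exact binomial distribution no cut-off at 54 meets both stated error rates. This needs no assumption about the decision rule.

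The size of the miss depends on the rule.

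- With 46 of 54, α is 5.25% against 5%, a small excess, and power is met.
- With 47 of 54, power is 83.2% against 90%, a shortfall of 6.8 percentage points. β is then 16.8%, so a workflow that is truly feasible in 90% of patients would fail about one time in six instead of one in ten.

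The second figure assumes that success means an exact one-sided 95% lower limit above 75%. That is the natural counterpart of a one-sided 5% α, but it is inferred. Both figures assume 54 evaluable patients and a true rate of exactly 90%.

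The weight is moderate. The shortfall comes from discreteness in a single-arm feasibility study. On the stricter rule the error is towards a missed positive finding, with α at 2.4%, and not towards wrongly declaring the workflow feasible.

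**What to change.** Name the cut-off before the analysis and restate the exact operating characteristics in the Statistical design section. Either of these sentences would do at the present size:

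- The workflow is judged feasible if at least 47 of 54 patients succeed; exact one-sided α is 2.4%, and power is 83.2% at a true rate of 90%.
- The workflow is judged feasible if at least 46 of 54 patients succeed; exact one-sided α is 5.25%, power is 91.4%, and the one-sided 95% interval is not the decision rule.

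As an option, set the evaluable number to 55 with a cut-off of 47 (α 4.5%, power 90.6%), which meets both targets.

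The abstract gives 54 as the number to be recruited, while the Statistical design section needs 54 evaluable and removes non-eligible patients. An evaluable number of 55 would therefore be lost with a single exclusion. If exclusions are expected, the cut-off should be tabulated for each possible evaluable number; any number from 60 to 63 meets both targets.

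The cost is one sentence and a less favourable stated error rate, or one further evaluable patient.

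### The rule for leaving patients out of the ITT feasibility rate lists consent withdrawal as ineligibility and sets no time limit, so some workflow failures can drop out of the denominator

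*Protocol article*

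**What the plan says.** All references are to the protocol article.

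- **Question.** Study objectives: "The study will investigate what proportion of treatments can be completed in an MRI-only workflow".
- **Benchmarks.** Statistical design: the workflow counts as not sufficiently feasible "if the feasibility rate was 75% or less". A positive evaluation postulates that "this is the case in 90% of patients". The α-error "is said to be only 5" per cent, power is 90%, and 54 evaluable patients are needed under a one-stage Fleming design.
- **Exclusion rule.** Statistical design: patients who breach the inclusion criteria at the moment of inclusion are left out of the statistical analysis and described only as individual cases. The examples are "e.g. Unsuitable for MRI due to metallic implants, withdrawal of consent, immobilization without stereotactic mask".
- **Who decides.** A review described as blind, held before the analyses, settles which patients with serious protocol violations belong to this group.
- **Everyone else.** All remaining patients form the ITT set. The primary rate is feasible ITT patients over all ITT patients, with exact one-sided 95% and 90% confidence intervals.
- **Related text.** Exclusion criteria already bar patients with an MRI contraindication. Study design describes the trial as open and non-randomized. Table 1 lists six verifications made during planning and treatment; failing any one moves the patient to the CT-based workflow.

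**The concern.** The rule and its examples do not agree. The rule looks at a patient's status on entry. Consent is itself an inclusion criterion, so it was present on entry in anyone validly enrolled, and withdrawing it is a later event. Someone applying the examples as written would remove a patient who enrolled, could not get through the masked MRI and then withdrew. For a feasibility trial that patient is a non-completion, and the set that remains is still called ITT.

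The MRI example has a milder form of the same problem. A patient with a contraindication known before entry should not have been enrolled, and leaving that patient out is defensible. The text does not, however, restrict the example to what was known or documented beforehand. Metal first noticed at the study MRI could be handled as ineligibility or as a workflow failure.

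The blind review is a weak safeguard. There is no allocation to be blind to, and the verification results arise in the course of treatment, so they exist before any review that precedes the analyses. The article does not say that the reviewers are kept from them.

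The primary rate is at stake. It is the only hypothesis-bearing result, and it is compared with a fixed 75% limit.

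**Working it through.** **1. The plan's own sample size.** Inputs from Statistical design: p0 = 0.75, p1 = 0.90, one-sided α = 0.05, power 0.90.

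n = [(1.645·√(0.75·0.25) + 1.282·√(0.90·0.10)) / (0.90 − 0.75)]² = 53.46, rounded up to 54. The stated figure is reproduced.

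**2. Decision rule.** The article gives no cut-off count. I take success to mean that the exact (Clopper-Pearson) one-sided 95% lower bound lies above 75%.

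| Result | Rate | Lower bound | Above 75%? |
|---|---|---|---|
| 46/54 | 85.2% | 74.85% | no |
| 47/54 | 87.0% | 77.0% | yes |

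The cut-off is therefore 47. Its exact chance of success at 75% is 2.4%. A cut-off of 46 would give 5.25%, just over the planned 5%.

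**3. Can one patient matter?** Take 46 successes among 54 enrolled patients and remove one failure as non-eligible.

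- 46/54: lower bound 74.85%, not above 75%.
- 46/53: lower bound 76.6%, above 75%.

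The conclusion reverses. It does not do so everywhere: if 47/54 is observed after one failure was dropped, restoring that patient gives 47/55 with a lower bound of 75.3%, still positive.

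**4. Effect on the false-positive chance.** Assumptions, none of them given in the article: true feasibility among all enrolled patients is 75%; a share f is dropped; every dropped patient is a failure; 54 patients remain in the analysed set. The analysed rate is then 0.75/(1 − f), and the chance of success is P(X ≥ 47) for a binomial with n = 54 and that rate.

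| f | Analysed rate | P(X ≥ 47) |
|---|---|---|
| 0 | 75.0% | 2.4% |
| 2% | 76.5% | 4.2% |
| 3% | 77.3% | 5.5% |
| 5% | 78.9% | 9.4% |

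The planned 5% is passed at roughly 3% dropped. With a cut-off of 46 the same four values are 5.25%, 8.55%, 10.8% and 17.0%.

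**5. Direction.** Removing a failure lowers the denominator and leaves the numerator alone, so the rate rises. Removing a patient who would have succeeded lowers it. The bias is upward only to the extent that removed patients would have failed.

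**The case against.** The stated rule turns on status at inclusion, the removed cases are still reported individually, and leaving out patients who should never have been enrolled is ordinary practice. All of this stands, and it is why the MRI example needs a time limit rather than deletion.

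Four stronger readings may tempt a reader. The article does not support them.

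- **That the planning rate counted withdrawals as failures.** It came from a retrospective review that names claustrophobia, metal artifacts or a glass eye, and one reconstruction problem. Withdrawal does not appear.
- **That the rule removes the metal cases counted in planning.** Those patients had already had a radiotherapy simulation MRI and were judged unsuitable because "they had metal artifacts on the skull due to surgery or had a glass eye". The exclusion example concerns patients who should not enter the MRI at all. A scanned patient whose artifact spoils the sCT fails Verification 1 and stays in the denominator.
- **That claustrophobic patients are removed.** The planning review says "5% of patients were not suitable due to claustrophobia", but claustrophobia is not among the exclusion examples. Such patients stay in as failures by default, unless they withdraw or are classed as having another patient-specific contraindication. Treating the whole planning shortfall of about 9% as droppable therefore has no basis.
- **That exclusions leave the trial short of patients.** The Abstract says "A total of 54 patients with an indication for radiation treatment of the brain and stereotactic mask immobilization will be recruited", but Statistical design states the requirement correctly as 54 evaluable patients, and replacement rules may stand in the full protocol. Exact power is also saw-toothed: against 90% it is 83.2% at n = 54 (cut-off 47) and 87.8% at n = 50 (cut-off 43), so a figure for one smaller n says little.

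It is also fair that dropping 2% keeps the false-positive chance within 5% at a cut-off of 47, and that the article gives neither a withdrawal rate nor reasons for withdrawal.

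**Conclusion.** The point holds in limited form. Withdrawal of consent is wrongly listed as ineligibility on entry, the MRI exclusion has no time limit, and the review that applies both is not shown to be shielded from known outcomes. Followed as written, this lets some workflow failures leave the primary denominator.

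The size cannot be derived from the article. The increase from 2.4% to between 4.2% and 9.4% rests on an assumed 2% to 5% dropped, all of them failures, and on a cut-off of 47/54. The firmer result is the sensitivity: near the decision limit, reclassifying one patient is enough to change the conclusion. It would be wrong to infer that the rate will be biased by a known amount, or that the planning failures as a group are removed.

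**What to change.** In Statistical design:

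1. Remove withdrawal of consent from the examples of ineligibility.
2. Limit exclusion from the primary set, including for MRI unsuitability, to breaches of a listed criterion that existed and were documented before the first study MRI.
3. Count every other enrolled patient who does not complete the MRI-only workflow as not feasible, including withdrawals after enrolment. Where withdrawn consent prevents use of a patient's data, add a worst-case analysis that counts the patient as a failure.

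The cost is a change of wording. The observed rate may be slightly less favourable, and a withdrawal unrelated to the workflow will count against it; reporting the reasons for withdrawal lets readers judge that.

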## Methods

### Study design

This study is an open, mono-centric, non-randomized, prospective study to evaluate feasibility of an MRI-only workflow providing accurate treatment planning and patient positioning. Patients eligible for the sCT-Feasibility trial require an indication for brain radiotherapy in either the definitive or postoperative setting and must have no MRI contraindications.

Each participant of the study will undergo the standard of care imaging for treatment planning, consisting of both MRI and CT scans, each performed within five days before the commencement of treatment. However, within the study the treatment will be based on MRI-only, i.e. treatment planning and positioning of the patients with 2D/2D imaging at the linear accelerator will be based on synthetic CT data. Feasibility of such a workflow will be evaluated en route by verification against the standard treatment as schematically outlined in Fig. 1 and described in detail in Sect. 2.4.

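### The review that removes non-eligible patients from the primary denominator is not tied to baseline data or dated before the verification results, so the rule permits outcome-aware exclusions

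*Protocol article*

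**What the plan says.** Under Statistical design, the protocol article removes one group from the analysis and reports it only as individual cases: "Patients who show a violation of the inclusion criteria at the time of inclusion in the study". Its examples are: "Unsuitable for MRI due to metallic implants, withdrawal of consent, immobilization without stereotactic mask". Of membership it says: "Which patients with serious protocol violations fall into this category is decided prospectively". This is to happen in a blind review, and the only timing given is "before the analyses are carried out". All other patients form the intention-to-treat set. The primary criterion is the number of feasible patients in that set divided by the size of the set, with exact one-sided 95% and 90% confidence intervals.

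Under Study design: "This study is an open, mono-centric, non-randomized, prospective study". The caption of Table 1 (Study plan) says: "In case a verification fails, the patient is transferred from the MRI-only workflow to the standard workflow based on CT". The Fig. 1 legend describes the same checks and change of workflow during treatment.

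**The concern.** In a randomised trial, a blind review of the analysis sets protects the result because the reviewers do not know the allocation. Here there is one arm and no allocation to conceal. What would need concealing is the outcome, meaning whether the patient stayed in the MRI-only workflow. A failed verification changes the patient's workflow on the spot, so the treating team knows the outcome as it occurs. Holding the review before the analysis adds little, because the analysis is a count of outcomes already seen.

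The boundary of the category is also soft in two places.

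- **Consent withdrawal** is listed as a violation at inclusion, yet it can come later, including after a failed step.
- **Metal-related MRI unsuitability** lies close to what the planning data counted as infeasibility. In the retrospective series, 5% were unsuitable because of claustrophobia and a further 4% for reasons such as "they had metal artifacts on the skull due to surgery". Together these make up 9 of the roughly 10 percentage points of expected infeasibility. A similar case in the trial could be counted as a failure or set aside as ineligible.

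If that choice is made with the outcome known, the primary denominator depends on the result and the planned error rate no longer applies as stated.

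**Working it through.** **Inputs** (Statistical design): unacceptable rate p0 = 0.75, expected rate p1 = 0.90, one-sided α = 0.05, power 0.90, n = 54 evaluable, exact one-sided intervals.

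**1. The plan's sample size.** With the one-stage normal approximation,

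n = [(z0.95·√(p0(1−p0)) + z0.90·√(p1(1−p1))) / (p1−p0)]²
= [(1.645 × 0.4330 + 1.2816 × 0.3000) / 0.15]² = 53.46, rounded up to 54. The stated figure reproduces.

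**2. Decision rule with all 54 kept.** The article does not say which interval decides. I take success as an exact (Clopper-Pearson) one-sided 95% lower limit above 0.75, which matches the stated 5% error. The smallest passing count is then 47/54 (at most 7 failures), with P(X ≥ 47 | n = 54, p = 0.75) = 0.0241.

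**3. Effect of removing failures from numerator and denominator.**

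| Result | Failures | Exact p against 0.75 | 95% lower limit | Positive? |
|---|---|---|---|---|
| 46/54 | 8 | 0.0525 | 0.7485 | no |
| 46/53 (one removed) | 7 | 0.0283 | 0.7662 | yes |
| 45/54 | 9 | 0.1009 | 0.7272 | no |
| 45/52 (two removed) | 7 | 0.0332 | 0.7620 | yes |

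**4. Worst-case type I error.** At n = 54, 53, 52 and 51 the exact rule allows at most 7 failures. If up to k failures are removed whenever that helps, the trial passes with up to 7 + k failures among the 54, so the type I error is P(X ≥ 47 − k | n = 54, p = 0.75):

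| k | Type I error |
|---|---|
| 0 | 0.0241 |
| 1 | 0.0525 |
| 2 | 0.1009 |
| 3 | 0.1735 |

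**5. How often one removal decides.** It needs exactly 46/54. At a true 75% the probability is 0.0525 − 0.0241 = 0.0284. At a true 90% it is 0.9138 − 0.8321 = 0.0817.

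**6. Other readings of success.**

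- On the 90% interval, 46/54 already passes (limit 0.7705). The flip moves to nine failures: 45/54 has limit 0.7497 and 45/53 has 0.7664.
- If success means an observed rate of at least 90%, 48/54 = 88.9% fails and 48/53 = 90.6% passes.
- If an excluded failure is replaced by a success to restore 54, 46/54 becomes 47/54, which passes (p = 0.0241).

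**The case against.** A reader might infer that the review cannot be blind in an open single-arm study, or that every reviewer will know the outcomes. The text does not support either. Reviewers given only eligibility data would be blind to the verification results. The article does not say who reviews or what they see, and such detail may stand in the full protocol.

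A reader might also take the phrase on serious protocol violations as open licence to drop anyone. It is not. It refers back to a category defined by violations at inclusion, most eligibility criteria are documentable baseline facts, and a failed verification is not a listed ground for exclusion. Removing a truly ineligible patient on baseline data alone does not bias the result.

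On size, the one-removal flip needs exactly eight failures, at least one of them in a patient who can be classed as ineligible. It takes the worst-case error only to 0.053, close to the planned 5%. Larger inflation needs two or more such patients, and nothing in the article suggests how often that would happen.

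All of this stands and limits the claim. It does not remove it, because the article does fix the timing, and fixes it by the analysis rather than by the outcome. Two of its three examples also sit on the boundary between ineligibility and failure.

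**Conclusion.** The concern holds in a limited form. As written, the rule allows patients to leave the primary denominator after their outcome is known to the treating team; it does not show that this will happen. One excluded failure can change the conclusion in a borderline result (46/54 to 46/53). The type I error of 0.053, 0.101 or 0.174 for up to one, two or three removals is an upper bound, not a forecast.

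These figures assume that success means an exact one-sided 95% lower limit above 75%, that 54 patients are enrolled, that excluded patients are not replaced, and that failures are removed whenever this helps. On the 90% interval or an observed-rate criterion the flip occurs at a different count but does not disappear. The point deserves correction because the primary result is a single proportion in 54 patients and the remedy is cheap.

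**What to change.** 1. Judge non-eligibility only from inclusion and exclusion facts present at enrolment, recorded with a date before Verification 1 for that patient. Where such a fact is found late, have it judged by reviewers who do not see the verification results.
2. Keep in the primary denominator every patient who leaves the MRI-only workflow after enrolment, including for MRI unsuitability. Where withdrawal of consent after enrolment forbids use of the data, report the number and timing of these cases.
3. Add a sensitivity analysis that counts every excluded enrolled patient as not feasible.
4. Replace the unexplained term blind review with a statement of who decides, on which data and when.

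The cost is one dated eligibility entry per patient, one extra analysis, and possibly a slightly lower stated feasibility rate.
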